#### 2.9.2. Changes of sedentary behavior

Sedentary behavior will be assessed by three indicators including total daily sedentary time, prolonged sedentary time (time spent sitting >30 minutes and >60 minutes), and number of sit-to-stand transitions. These three sedentary behaviors will be measured by 7 days of activPAL 3 (PAL Technologies, U.K) device monitoring prior to the beginning of the intervention/control protocol and again after the conclusion of the protocol for both study arms. The activPAL 3 monitor is a tri-axial accelerometer that also includes an inclinometer, worn on thigh (Fig 4). Due to the activPAL 3 position on the thigh, the activPAL 3 monitor is the most sensitive device to distinguish sitting (horizontal position) and standing (vertical position) [43, 44]. The activPAL 3 has demonstrated great test-retest reliability and criterion validity with direct observation to classify sitting, standing, and stepping [45].

**Fig 4 pone.0302582.g004:**
[figure not shown]
Participant wearing activPAL 3 on thigh for sedentary behavior and physical activity measurement.

### 2.10. Secondary outcomes

#### 2.10.1. Physical activity

Time spent standing and walking (stepping), number of sitting-to-standing transitions, and number of step counts will be measured using the activPAL 3 device. The activPAL 3 has demonstrated greater criterion validity compared to video observation for measuring physical activity [46].

#### 2.10.2. Cardiometabolic markers

Height, weight, and waist and hip circumferences will be measured using a validated stadiometer, digital scale, and flexible tape measure, respectively. All measurements will be recorded to the nearest 0.1 cm and 0.1 kg. Blood pressure will be measured using an automated and validated blood pressure monitor. The device will take three readings at 2-minute intervals and the mean of three BP readings will be recorded. For blood samples, participants will be required to fast overnight (at least 8 hours). Cardiometabolic markers including fasting lipids, insulin levels, HbA1c, and hs-CRP levels will be collected via finger prick by a trained research staff member, using dried blood spot cards for measurement and analysis at ZRT Laboratory (Beaverton, OR, U.S.A). Lastly, 24-hour glucose levels will be measured by the use of a continuous glucose monitor (Freestyle Libre 2, Abbott, U.S.A) over a 7-day period at baseline and post-intervention. The 24-hour glucose control will be evaluated by mean 24-hour glucose levels, glucose management indicator, glycemic variability (%), % time below range (glucose < 70 mg/dL), % time in range (glucose 70–180 mg/dL), and % time above range (glucose >180 mg/dL) [47].

#### 2.10.3. Patient-centered outcomes

Confidence in reducing sedentary behavior will be measured using the 12 items from the Self-Efficacy Questionnaire for Physical Activity and Sedentary Behavior (previously reported Cronbach’s α = 0.79) [48]. The items assess the level of confidence for specific sitting behaviors and sedentary breaks. Habit strength for sedentary behavior will be assessed by using the validated Self-Report Habit Index measure (previously reported Cronbach’s α = 0.91) [49]. This 7-item index was adapted to assess the degree to which sedentary breaks (standing/walking) become habitual [49]. Fear of movement will be measured by using the Fear Avoidance Belief Questionnaire. The questionnaire consists of 5 items regarding patients’ beliefs about the relationship between perceived discomfort and movement, which can lead to fear of movement and avoidance of physical activity/exercise. The words “pain” and “back” were changed to “heart discomfort” and “heart” respectively, as used by Ahlund et al. [50]. The questionnaire was also validated for patients with CVD. Depressive symptoms will be measured using the Patient Health Questionnaire 9 (PHQ-9) [51].

### 2.11. Demographic characteristics and potential covariates

We will collect standard demographics, socioeconomic characteristics, medical history, and current medication via self-report. We will also ask about current occupation activity, which ranges from “mostly sedentary” (e.g., desk-based job) to “very active and physical” (e.g., manual labor). Participants will answer questions about their tobacco use, alcohol intake, dietary habits as measured by the 16-item Rapid Eating and Activity Assessment for Participants Short Version (REAP-S) [52], and sleep quality as measured by the 10-item Pittsburgh Sleep Quality Index (PSQI) [53].

### 2.12. Data management plan

Study participants will complete questionnaires online via REDCap, and the study team will review the responses in the presence of the participants to clarify or complete any missing information. REDCap, a secure, HIPAA-compliant web-based application developed at Vanderbilt University, will be used to manage all data. It provides data entry, audit trails, and export procedures, and flags inconsistent or out-of-range responses for review.

### 2.13. Analysis plan

Feasibility (dropout rates and intervention compliance) and acceptability outcomes (assessed by satisfaction questionnaires) will be calculated and reported as percentages. The determination of whether the Sit Less program is feasible and acceptable will be based on the previously defined criteria. The recorded exit interview will be transcribed verbatim and analyzed using a thematic approach to guide refinements to future sedentary behavior reduction interventions as well as to identify barriers and facilitators to sedentary behavior reduction. To enhance credibility, we will follow the consolidated criteria for reporting qualitative research (COREQ) guidelines [54].

For sedentary behavior and light PA data from the activPAL 3, we will only include data of daily wear time >10 hours, with a minimum of 4 valid days [37]. The activPAL data will be downloaded and analyzed by using the activPAL 3 processing software and applying “CREA (enhanced analysis algorithm)” processing setting (PAL analysis, V8.11, PAL Technologies). The CREA algorithm demonstrated excellent agreement with diary data [55] and strong correlation with using a traditional algorithm to assess wake time activities [56].

Once all the data from activPAL 3 have been processed, statistical analyses will be conducted using STATA 18 (StataCorp, U.S.A). All analyses will adhere to an intention-to-treat approach, and there will be no imputation of data. Given this simple pre-post design, participants in both study groups without a post-intervention value for a respective outcome measure will not be included in the analysis of effects on that measure. Demographic and other baseline values will be compared between those who do and do not complete the study to inform potential modifications to the intervention for future studies. Descriptive statistics will summarize the demographic and clinical characteristics of the participants. Chi-Square, Mann-Whitney or independent *t*-tests will be used to inform potential differences between control and intervention groups at baseline. We will consider sex as a biological variable and conduct subgroup analyses to determine if there are differences in sedentary behavior outcomes and the acceptability of the Sit Less program.

We will use generalized linear models to assess the effects of the intervention on the key study outcomes. We anticipate that most will use the Gaussian family of distributions with the log link function, yet some are likely to be severely skewed or demonstrate a better fit using the Poisson family or nonparametric regression models. Estimated mean differences in the post-intervention values controlling for the baseline assessments will be generated from each respective outcome model. These estimated adjusted mean differences will be used to evaluate the effect of the study group and to serve as measures of effect sizes. For example, if the Sit Less group sits for 60 minutes less than the control group after the intervention, this is crucial to comprehending the effects of the intervention and to inform the design of future large-scale RCTs. Furthermore, we will generate bootstrapped 95% confidence intervals around each adjusted mean difference. All models and estimations of adjusted mean differences will use the robust or sandwich estimator of variance. While we will consider results statistically significant if p < 0.05, we will not adjust this critical alpha level for the multiple outcomes assessed in this work, as the focus is on the estimated mean differences for informing future work.

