## Introduction

Cardiovascular disease (CVD) remains the leading cause of death in the U.S. Half of people who survive a heart attack suffer a second heart attack within three years [1], and 15% die from recurrent heart attacks [2]. Moderate-to-vigorous levels of physical activity (PA) can significantly reduce reinfarction and cardiac mortality [3], and therefore, moderate-to-vigorous levels of PA >150 minutes per week is recommended for CVD patients [4, 5]. However, only 10–21% of CVD patients meet the PA recommendations [6, 7] and they still spend 10–11 hours on sedentary behavior [6, 8–10]. Common barriers to physical activity include fear of reinfarction, shortness of breath, fatigue [11, 12], and time and cost related to exercise [12, 13]. Thus, there is an urgent need to find innovative ways of engaging this population in achieving more active lifestyles.

In people with CVD, sedentary behavior takes up to 70–90% of waking activities [6, 8–10] and 50% of sedentary behavior is prolonged (>30 minutes per bout) [8]. During sedentary time, there is no muscle contraction of the legs, which causes decreasing insulin sensitivity, vascular dysfunction, and activation of low-grade inflammatory cascades [14]. As a result, greater total sedentary time is related to increased CVD risk [15], including decreased high-density lipoprotein (HDL) and increased triglycerides (TG), fasting glucose [16], BMI, and waist circumference (WC) [17]. Prolonged sedentary time is also associated with a 12% higher risk of incidental CVD [18] and an increased risk of CVD mortality regardless of PA levels [19, 20].

Reducing sedentary time with frequent bouts of standing or walking is safe and feasible for patients with chronic diseases [8, 21, 22]. Emerging evidence from meta-analyses and intervention studies conducted in free-living environments indicate significant beneficial relationships of sedentary breaks with BMI, waist circumference, and C-reactive protein (CRP) [23], as well as average glucose levels, insulin and blood pressure (BP) [23–25]. Therefore, frequent sedentary breaks can not only reduce the total sedentary time and increase total standing and walking time, but also break prolonged sitting time, bringing additional cardiometabolic benefits and possibly overcoming common barriers to moderate-to-vigorous PA.

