### 2.6. Intervention

The 12-week intervention (Sit Less program) will consist of four components based on the Habit Formation framework (Fig 3). Previous studies have shown significant (91 minutes/day) reductions in sedentary time following 4 to 24 weeks of intervention [29].

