## Discussion

The study aims to evaluate a multi-technology-based and individually tailored intervention to reduce sedentary behavior in CVD patients. The primary outcomes are the feasibility, acceptability, and primary efficacy in changing sedentary behavior (change in total minutes spent in sedentary behavior, change in prolonged sedentary time, and number of sit-to-stand transitions) measured by the activPAL. Secondary outcomes are changes in physical activity measured by the activPAL and changes in cardiometabolic biomarkers measured by CGM and dried blood spot cards, along with changes in psychosocial constructs.

Despite the important role of sedentary behavior in cardiac outcomes in CVD patients, there are few studies focusing on reducing sedentary behavior in this understudied population. In this study, we will test a sedentary behavior reduction intervention program based on habit theory that leverages wearable technology, for CVD patients. The proposed sedentary behavior reduction program is innovative because it side-steps barriers of exercise (e.g., fear of heart discomfort, fatigue) in CVD patients and focuses on breaking sedentary time with short bouts of standing and walking, which can be easily implemented in the natural environment. Other novel aspects of this study include using multiple technologies, including a Fitbit and a smart water bottle to motivate participants to stand up, and the development of an automatic, yet tailored text message algorithm. The study will also employ a validated measure for sedentary behavior (i.e., activPAL) and sensitive biological indicators linked to sedentary behavior, such as 24-hour glucose monitoring parameters.

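### Sedentary time is analysed in total minutes on any activPAL day above 10 hours of wear, with no wear-standardised analysis alongside, so a wear difference between arms would read as a sitting difference

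*Protocol article*

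**What the plan says.** Section 2.9.2 names three activPAL measures: "total daily sedentary time, prolonged sedentary time (time spent sitting >30 minutes and >60 minutes), and number of sit-to-stand transitions". The Discussion gives the scale of the first as "change in total minutes spent in sedentary behavior".

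Section 2.13 sets the validity rule: "we will only include data of daily wear time >10 hours, with a minimum of 4 valid days". It gives no upper limit on wear, no denominator and no standard day length. The model is described in the same section: "Estimated mean differences in the post-intervention values controlling for the baseline assessments will be generated from each respective outcome model". Wear time is not named there, nor among the potential covariates in 2.11. The removal of sleep and the 10-hour rule in 2.6.5 concern the Fitbit data behind the text messages, not the activPAL outcome.

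For scale, the Introduction reports "In people with CVD, sedentary behavior takes up to 70–90% of waking activities" and, of the same patients, "they still spend 10–11 hours on sedentary behavior". Section 2.13 uses a 60-minute difference as an example, and 2.6 cites a 91 min/day reduction from earlier studies.

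**The concern.** Under this rule a day with just over 10 hours of wear and a day with many more hours both count in full. Sitting can be recorded only while the device is worn, so the outcome mixes two things: how much of the time a person sits, and how much of the day was observed. If one arm is observed for longer at follow-up, its total minutes rise with no change in behaviour.

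There is a conceivable route to such a difference. Participants know their allocation (2.5), and only the intervention arm spends 12 weeks with charge-and-sync messages, non-wear reminders and staff calls about a tracker (2.6.3). That could lengthen activPAL wear at follow-up and hide a benefit, or tire participants of devices, shorten wear and create an apparent benefit.

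At stake is the lead efficacy estimate, which 2.13 intends as an effect size for designing larger trials. A wear artefact, or avoidable noise, would carry into that planning.

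**Working it through.** **Inputs from the article.** Sedentary share of waking time p = 0.70 to 0.90, and 10–11 h of sitting, read as per day (Introduction); half of sedentary time in bouts over 30 min (Introduction); valid day above 10 h (2.13); 35 per arm (2.2); example effect 60 min (2.13); earlier studies 91 min/day (2.6). The article gives no wear-time distribution, so wear SDs and correlations below are assumptions.

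**1. Background figures against the validity rule.** Implied waking day = sitting hours / p. The extremes are 10/0.90 = 11.1 h and 11/0.70 = 15.7 h. A day with 10 h of wear yields 10 × 0.70 = 7 h to 10 × 0.90 = 9 h of sitting, less than the 10–11 h expected. A barely valid day therefore understates total sitting for a typical patient.

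**2. Single days.** Spurious difference = wear difference × p. For 10 h against an assumed 13 h: 180 × 0.70 = 126 to 180 × 0.90 = 162 min. This describes two days or two people, not two arms.

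**3. Arm means.** The same formula applies to the difference in mean waking wear:

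| Arm difference in mean wear | Spurious sitting difference |
|---|---|
| 30 min | 21–27 min/day |
| 60 min | 42–54 min/day |

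Inverting it, a 60-minute artefact needs 60/0.90 = 67 to 60/0.70 = 86 min of wear difference. A 91-minute artefact needs 101 to 130 min.

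For bouts over 30 min, with half of sedentary time prolonged and the same mix in the extra hours, a 60-min wear difference gives 60 × 0.70 × 0.5 = 21 to 60 × 0.90 × 0.5 = 27 min. The article gives no transition rate, so no figure follows for transitions.

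**4. Chance imbalance.** The standard error of the arm difference in wear is SD × √(2/35). For assumed wear SDs of 60, 90 and 120 min, the 95% limits are about ±28, ±42 and ±56 min of wear, or 20–25, 30–38 and 39–51 min of sitting. At p = 0.8, the probability that chance alone yields 60 min or more of sitting is under 1% in each case.

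**5. Noise after baseline adjustment.** Assumptions: mean wear 840 min, mean share 0.80, share SD 0.07 with correlation 0.6 between visits, wear SD 60 min with correlation 0.5, share and wear independent, linear model.

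- Wear part of the variance: (0.80 × 60)² = 2,304. Share part: (840 × 0.07)² = 3,457. Total: 5,761.
- Correlation of raw minutes between visits: (0.5 × 2,304 + 0.6 × 3,457)/5,761 = 0.56.
- Raw minutes, adjusted: √[(2/35) × 5,761 × (1 − 0.56²)] ≈ 15 min.
- Standardised, adjusted: √[(2/35) × 3,457 × (1 − 0.6²)] ≈ 11 min.

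With wear SD 30 and correlation 0.8, the raw figure is about 12 min. With SD 90 and correlation 0.2 it is about 21 min. The standardised figure stays at about 11. Simulation under the central assumptions gave the same 15 and 11 min. With a 30-min arm difference in follow-up wear and no true effect, it gave about 24 min of false effect in raw minutes and essentially none when standardised.

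**The case against.** The strongest reply is that this is detail an article leaves to the analysis plan. Section 2.13 does not say that baseline is the sole adjustment, and nothing excludes a wear-time covariate or denominator. That stands as a limit: a reader might infer that wear adjustment has been ruled out, and the article does not support that. But the article does fix the scale, the wear threshold, the processing algorithm and the adjustment it names, and together these describe an outcome that moves with wear.

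Several stronger readings also fail.

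- **That wear could reproduce the trial's target effect.** There is no target effect. Section 2.2 says the sample size was not based on effect sizes, 60 min is introduced as an example, and the 120 min in 2.6.2 is a participant's own goal.
- **That clinic removal at baseline and mail-back at follow-up biases the comparison.** Both procedures apply to both arms (2.4.2, 2.8). A shift in wear common to both arms cancels in the contrast.
- **That the large differences between single days carry over to arms.** Arm means of multi-day averages differ far less, and chance alone is very unlikely to produce 60 min.
- **That tracker reminders will change activPAL wear.** The reminders concern a different device, and neither the direction nor the existence of an effect is shown.

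Section 2.14.1 also provides for checking activPAL data on return and re-taking measures when quality is poor. That offers some protection against failed recordings, but it does not equalise wear among valid days.

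Finally, absolute minutes match the participant goals and the earlier evidence, and a proportion is a different quantity. This stands, and is why total minutes should be kept.

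**Conclusion.** The point holds as a risk to the interpretation of the sedentary outcomes, not as a demonstrated bias. Total minutes with a wear floor of 10 h and only baseline adjustment named leave the arm contrast exposed at 0.7 to 0.9 min of sitting per minute of difference in mean waking wear. A 30-min wear difference would equal 35–45% of the article's 60-min example (21/60 to 27/60). Mimicking the whole example would need 67–86 min, for which there is no evidence.

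Balanced wear variation costs precision only. Under the assumptions in the working, the SD of the adjusted arm contrast falls from about 15 to about 11 min with standardisation. The gain ranges from very small to large, depending on the assumed wear SD and its correlation between visits.

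The calculations assume that the sedentary share is the same in worn and unworn waking hours. If it is not, standardising removes only part of the artefact.

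**What to change.** Keep total minutes, and pre-specify the following beside them:

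- Sedentary and prolonged-sedentary time as a percentage of waking wear time, or as minutes standardised to the sample's mean waking wear. A fixed 16-h day is a poor reference, because it lies above the whole 11.1–15.7 h range implied by the article's own figures.
- Sit-to-stand transitions per waking hour. A rate per sedentary hour should be avoided, because its denominator is what the intervention aims to reduce.
- The same baseline-adjusted model for these measures, with wake and wear time taken from the activPAL processing already planned.
- Mean waking wear reported by arm and visit.
- An interpretation rule: read the raw-minute difference as a change in sitting only if the standardised result agrees.

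The cost is one derived variable per outcome and a sentence explaining that a proportion is a slightly different quantity from absolute minutes. No new data collection should be needed.

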### 2.5. Randomization

By using the REDCap randomization module, computer-generated random numbers will be created by a statistician. During Baseline Visit 2, randomization to the intervention and control arms (1:1) will be performed by a study team member. A study team member will click REDCap’s randomization function and each participant’s group assignment will be available online via REDCap. The study team member will immediately inform participants of their group assignment during Baseline Visit 2. Participants and interventionist will not be blinded to the allocation due to the nature of the intervention program. However, outcome assessors and data analysists will be blinded to the allocation.

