### 2.14. Oversight and monitoring

#### 2.14.1 Data monitoring

As a single-site, low-risk behavioral study, we will not establish a Data Safety and Monitoring Board, nor conduct interim analyses. Instead, the PI (CP), supervised by the coauthor (SM) and aided by the study team, will bi-monthly monitor enrollment, data quality, adverse events, and participant dropout rates. Data from the continuous glucose monitoring and activPal devices will be assessed for validity immediately after return. Should data quality be below standards, the team will review the monitoring protocols and measures will be re-taken accordingly.

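### Analyses labelled intention-to-treat exclude every participant without a post-intervention value; this is an available-case analysis by randomised arm, and it is biased if missingness depends on the outcome beyond arm and baseline

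*Protocol article*

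**What the plan says.** All references are to the protocol article. Section 2.13 (Analysis plan) sets the analysis population in two adjacent sentences. The first is "All analyses will adhere to an intention-to-treat approach, and there will be no imputation of data". The second, which gives the simple pre-post design as its reason, says that "participants in both study groups without a post-intervention value for a respective outcome measure will not be included in the analysis" of that measure.

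Two further rules decide who has a value. For activPAL outcomes, "we will only include data of daily wear time >10 hours, with a minimum of 4 valid days". The effect estimate is also conditional on baseline: "Estimated mean differences in the post-intervention values controlling for the baseline assessments will be generated from each respective outcome model".

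One comparison touches on loss: "Demographic and other baseline values will be compared between those who do and do not complete the study". Its stated purpose is to guide changes to the intervention, and it is not linked to the effect estimate.

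On the baseline record, section 2.14.1 says "Should data quality be below standards, the team will review the monitoring protocols and measures will be re-taken accordingly". Section 2.5 says "The study team member will immediately inform participants of their group assignment during Baseline Visit 2", which is the visit at which, under section 2.4.2, the baseline activPAL is taken off.

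**The concern.** Intention-to-treat normally implies two things: participants are analysed in the arm to which they were randomised, and all randomised participants count in the estimate. The plan keeps the first and gives up the second, outcome by outcome, under a label that claims both. A reader of the results paper would take the adjusted difference to describe all 70.

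Informative loss is plausible in this design. Only the intervention arm has 12 weeks of Fitbit, smart bottle and three texts a week; controls receive usual care and fact sheets. The post-intervention activPAL outcome needs a further week of home wear and return by mail, then enough valid days, so a participant can attend week 13 and still be excluded. Dropout in section 2.9.1 counts only withdrawal of consent, so the reported rate can be lower than the share missing from the effect analysis.

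At stake is the size of the effect. Change in sedentary behavior is listed among the primary outcomes (section 2.9.2 and Discussion), and section 2.13 intends the adjusted differences as effect sizes for designing large trials. If participants who disengage from the program are the ones without data, those differences are too large.

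**Working it through.** **The plan's own figure.** Section 2.2 says that 30 participants are needed to see a problem of 10% probability with 95% confidence. ln(0.05)/ln(0.90) = 28.4, rounded up to 29. At n = 30 the detection probability is 1 − 0.9^30 = 95.8%. The figure is sound, and the present point does not depend on it.

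**Inputs from the article.** 35 per arm (section 2.2); an example difference of 60 min/day (section 2.13); post-intervention values adjusted for baseline, no imputation, exclusion per outcome (section 2.13).

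**Inputs assumed, because the article gives none.** Loss in the intervention arm, the effect in those lost, the SD of sedentary time and the baseline–post correlation.

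**Step 1: dilution.** Let a fraction d of the intervention arm be missing. Let completers show an effect E, let those missing have no effect, and let control losses be uninformative. The available-case difference is E. The difference over all randomised is E × (1 − d), so the overstatement is d × E. With E = 60 min/day:

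| d | All randomised | Overstatement | Relative, d/(1 − d) |
|---|---|---|---|
| 10% | 60 × 0.90 = 54 | 6 | 11% |
| 20% (7 of 35) | 60 × 0.80 = 48 | 12 | 25% |
| 25% | 60 × 0.75 = 45 | 15 | 33% |

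**Step 2: when does loss cause bias?** A simulation applied the available-case, baseline-adjusted regression to 35 per arm, with a true difference of −60 min/day, correlation 0.6, about 25% intervention loss, 10% control loss and 4,000 runs per scenario.

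| Loss in the intervention arm | SD 80 | SD 100 | SD 120 |
|---|---|---|---|
| Random | −59.9 | −60.8 | −59.6 |
| Depends on baseline only | −60.6 | −59.8 | −60.4 |
| Depends on the post-intervention value | −71.4 | −73.9 | −77.3 |

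The Monte Carlo standard error is 0.27 to 0.41. The first two rows show no bias, although loss is 25% against 10%. The third overstates by about 11 to 17 min/day. So the driver is dependence on the outcome beyond arm and baseline, not the imbalance in loss. The simulation used an identity link; the plan expects a log link for most outcomes.

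**Step 3: scale against sampling error.** With correlation 0.6 the residual SD is 0.8 × SD, or 64 to 96 min/day for SD 80 to 120. With 35 per arm the 95% half-width is 1.96 × residual SD × √(2/35), which is 1.96 × 64 × 0.239 = 30 to 1.96 × 96 × 0.239 = 45 min/day. A shift of 6 to 15 min/day lies inside that interval. But it is systematic, and it would carry over into the planning of the next trial.

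**Step 4: the order of events at baseline.** Section 2.4.2 removes the activPAL at Baseline Visit 2, section 2.5 randomises and discloses the arm at that visit, section 2.6.2 holds the goal-setting session there using the prior week's activPAL data, and section 2.14.1 allows poor data to be re-taken. None of these requires the validity check to come before randomisation.

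**The case against.** The strongest reply is that nothing is hidden. The label, the ban on imputation and the exclusion stand next to each other, and a careful reader knows who is analysed. Some authors use intention-to-treat to mean only analysed as randomised. A missing-data assumption and sensitivity analyses are often left to a statistical analysis plan. The study is a pilot sized on feasibility. It also takes steps against loss: $50 for the post-intervention visit and $50 for mailing the devices back, in both arms; reasons for dropout; staff review of questionnaires; and regular monitoring of dropout.

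Much of this stands, and it limits the weight. It does not rescue the label, because this article itself fixes both the label and the rule that departs from it.

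Stronger readings are tempting, and the article does not support them:

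- *Unequal dropout by itself biases the result.* It does not; step 2 shows estimates near −60 under random or baseline-only loss.
- *The trial's estimate is biased by 6 to 15 min/day.* The article gives no loss rate, and nothing shows that every missing participant gained nothing. Someone who attended but had too few valid days may well have responded.
- *Invalid baseline wear adds to the bias.* The first baseline wear precedes allocation, so the arm cannot have caused it. That loss costs precision.
- *The pre-post justification is wrong for a randomised trial.* The same sentence refers to both groups, and the phrase can fairly mean one baseline and one post-intervention measure. With a single post-intervention measure, imputing from arm and baseline alone would indeed add little.
- *Baseline measures will be re-taken after allocation.* The article does not say so. It leaves the order within Baseline Visit 2 open, so this is an inferred, secondary risk.

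**Conclusion.** The concern holds in a limited form. The plan calls its analyses intention-to-treat but specifies an available-case analysis by randomised arm, separately for each outcome. Whether the adjusted differences are biased depends on a mechanism that the data cannot reveal, and the design makes an informative one plausible. The overstatement is 6 to 15 min/day on a 60 min/day example if 10% to 25% of the intervention arm is missing with no effect. It is about 11 to 17 min/day in the simulated case of outcome-dependent loss, and about zero if loss is random or depends only on baseline. Loss, SD, correlation and the effect in those missing are all assumptions.

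Severity is moderate. The feasibility and acceptability conclusions are not affected by this point. What changes is how far the effect estimates can be relied on when a larger trial is planned.

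**What to change.** 1. **Label.** In section 2.13, replace the intention-to-treat claim with *available cases, analysed as randomised*, and state the assumption under which that is unbiased: missingness unrelated to the outcome given arm and baseline. Report the number analysed per arm for each outcome, separately from the consent-withdrawal rate. Cost: wording and one table row per outcome.

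2. **Sensitivity analysis.** Keep the available-case model as the main analysis, and limit the no-imputation sentence to it. Add an analysis of all 70 randomised in which missing intervention values are delta-adjusted or set by reference to the control arm; missing control values can be imputed from the baseline data. Report over a range of deltas, from no shift to complete loss of the effect. Multiple imputation or a mixed model using baseline data alone would add little and would not address outcome-dependent loss. Cost: a little more analysis work, and a choice of delta that cannot be tested, hence the range.

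3. **Secondary: baseline record.** At Baseline Visit 2, confirm that the activPAL record meets the valid-day rule before the REDCap randomisation is run, so that any baseline re-take under section 2.14.1 precedes allocation. The goal-setting session already requires the data to be read at that visit. Cost: a short check, and an occasional repeat baseline week. For participants already randomised, record whether any baseline was re-taken after allocation.
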